#### Co-interventions

Researchers emphasized to the managers that participation in other intervention studies or programs aimed at reducing occupational quartz exposure might influence the study results. Managers were therefore asked to not actively initiate other activities to decrease occupational exposure to quartz during the intervention period. After the intervention, managers are asked if any other intervention took place during the period of the current study.

#### Primary outcome measure

Respirable dust and quartz exposure are measured by collecting full-shift personal air samples from construction workers at different worksites
[22]. These samples are collected using Dewell-Higgins cyclones mounted with a PVC filter (Milipore, pore size 5.0 μm, diameter 25 mm), connected to a calibrated Gillian GilAir pump with an airflow of 2 l/min. Cyclones are attached in the breathing zone of the worker. The amount of dust on filters is determined gravimetrically by pre- and post-weighing of filters on an analytical balance in a conditioned room
[36]. Quartz is determined by infrared spectroscopy and X-ray diffraction
[37]. Throughout their shift, workers are observed using a structured walk-through survey to obtain detailed information on work activities (including task time), workspace, work practices, the type of tools used, type of material worked on, and respiratory protective equipment
[22].

#### Secondary outcomes

##### Behavioural determinants

Behavioural determinants related to respirable dust and quartz exposure are assessed by means of a questionnaire
[22].

Questions about beliefs, motivation, risk perception and social influence are formulated based on a structure of questions often applied in the assessment of behavioral determinants
[38]. Belief is defined as the indication of an individual’s belief in the effectiveness of various exposure controls and dust-reducing work practices, and is assessed by ten questions with answers on a 5-point scale. Additionally, motivation is measured by eleven questions with answers on a 5-point scale. Motivation is described as the indication of an individual’s intention (or motivation) to use exposure controls and dust-reducing work practices. Risk perception (six questions with answers on a 5-points scale) is defined as an indication of an individual’s perception of risk of quartz exposure and susceptibility to short- or long-term health effects. Lastly, three questions on a 5-point answer scale are constructed for social influence (i.e., indication whether an individual is influenced by co-workers or supervising personnel to use exposure controls and dust-reducing work practices).

An adapted format of an existing standardized scale is applied for risk propensity, which is an estimation of an individual’s inclination to seek or avoid general health risks
[39]. This scale consists of six questions with a range from 1 to 5.

Knowledge is described as an estimation of an individual’s knowledge regarding exposure sources, technical control measures, substances, routes of exposure and short- and long-term effect of quartz dust and is assessed by eight quartz dust-related questions which are specifically composed for the current study, with answers on a dichotomous scale.

##### Organizational factors

Managers of all participating companies receive a questionnaire in order to gain insight into the occupational safety and health policy
[22]. This questionnaire is based on the Occupational Health and Safety Assessment Series (OHSAS) norm for health and safety management, and specifically focuses on hazardous substances
[23]. The following themes were included: (i) the presence and compliance of work procedures and workplace instructions; (ii) the extent to which training and education is offered to employees; (iii) the presence of management support towards a proactive health and safety culture (e.g.., toolbox meetings on a fixed and regular schedule to stimulate discussion between managers and construction workers); and (iv) the method of communicating and providing feedback with equipment contractors to improve services.

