Third, organizational factors include the responsibility of companies and sector organizations for reducing high level of occupational quartz exposure. First, the availability of technical control measures at worksites is the responsibility of companies. However, the majority of managers face difficulties in collecting the relevant information about technical control measures from the different resources such as labour inspection and sector organization. They therefore recommend providing a clear overview of the newest technical control measures and their functionality. The majority of employers also mentioned the increasingly shorter lead times for construction processes, and working with subcontractors led to tighter bids. This resulted in less time and investments to use technical control measures at construction worksites. Additionally, managers are responsible for organizing training sessions to educate their construction workers about quartz exposure and technical control measures. Education, procedures, and training sessions at the worksites are of particular importance for the current study population, as most of them work without any professional education. The baseline study showed that only 25% of the managers offered this kind of training/education and five of eight (63%) companies stated that compliance with work procedures and workplace instructions regarding dust-reducing practices was supervised by their management
[22].

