#### Intervention program and materials

The first plenary session for all employees at the company (e.g., construction workers, managers and supervisors) was an interactive presentation by the principal researcher ([name]) and an occupational physician, consisting of the following elements: (i) showing a short documentary to increase risk perception and awareness of long-term health consequences; (ii) providing results of the baseline study, including both exposure and observed behavior; (iii) providing information regarding the health-risks; (iv) discussing situations with high quartz exposure; (v) teaching skills regarding the proper use of technical control measures by showing PIMEX videos (i.e., Picture Mix Exposure, a video exposure monitoring method for exposure of hazardous materials to measure the impact of workplace practices and conditions at the same time); (vi) discussing constraints and facilitators to work with technical control measures; and (vi) set tailored goals for the intervention period. At the end of this session, posters were distributed to companies and compact-sized factsheets are handed out to construction workers. For each job category, this tailored factsheet provides specific instructions on how to reduce quartz exposure at the worksite. These instructions are focused on (i) proper use of technical control measures; (ii) organizational factors such as asking the supervisor for technical control measures, and using protective equipment; and (iii) behavioral factors such as cleaning the workspace.

The second individual session is organized at the worksite and aims to teach workers how to use technical control measures in a proper and productive way. Therefore, the construction workers (i) define situations with high levels of exposure at their current worksite; (ii) learn how technical control measures should be used to reduce this exposure; (iii) discuss constraints for using technical control measures; and (iv) define solutions to tackle these constraints. At the end, an assignment is given to the construction workers in which they are asked to photograph two situations at the worksite (i.e., a good and a bad practice) which serve as input for the last plenary sessions.

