### Step 5: Development of a plan for implementation

Researchers pay attention in step 5 to important preconditions that ensure optimal implementation and adoption of the ‘Relieved Working’ study. Firstly, as managers and supervisors play a key role in successful implementing an intervention at worksites
[31], they are encouraged to actively participate in the intervention. Managers are also invited for a session with all participating companies to share ideas and learn about new innovations of technical control measures. Secondly, as time, place and costs are important factors to successfully adopt and implement the program
[32, 33], the three sessions are organized within the existing so-called “Toolbox Education system” in the Dutch construction industry. The toolbox education system consists of at least 10 obligatory health and safety training sessions for workers, which have to be organized by managers in the construction industry each year in order to obtain an official health and safety certificate. Thirdly, because the intervention is implemented across different companies, a protocol including an outline, time schedule, and communication between all stakeholders was developed to standardize the intervention.

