##### Effect evaluation

The potential difference between the baseline and follow-up values in the primary and secondary outcomes will be compared between the intervention group and the control group. Analyses of measurements at individual level (i.e., exposure assessment and questionnaire) will be performed by means of multi-level analyses taking clustering of observations of workers within the same company into account, as well as repeated measurements within one worker
[40]. Due to randomization at company level, the data will be analyzed at three levels: time, worker and company. The multi-level analyses using the follow-up measurement as dependent variable will be adjusted for possible confounding factors, such as education level and job category. These variables will also be checked for effect modification.

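### One of four organisational themes, training offered to employees, can rise through the trial's own training sessions without any change in company policy

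*Protocol article*

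**What the plan says.** The protocol article lists organisational factors among the secondary outcomes. Under Organizational factors it states: "Managers of all participating companies receive a questionnaire in order to gain insight into the occupational safety and health policy". Four themes follow:

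- (i) work procedures and instructions;
- (ii) "the extent to which training and education is offered to employees";
- (iii) management support for a proactive safety culture, with "toolbox meetings on a fixed and regular schedule to stimulate discussion between managers and construction workers" as an example;
- (iv) communication and feedback with equipment contractors.

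The intervention is largely training. Under Intervention program and materials, the first plenary session includes "teaching skills regarding the proper use of technical control measures by showing PIMEX videos". A worksite session on using control measures and a closing plenary session follow, and managers attend a separate demonstration. Step 5 adds that "the three sessions are organized within the existing so-called “Toolbox Education system” in the Dutch construction industry". Under Study design, the control group receives no intervention.

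The Co-interventions section reports that managers were asked not to start other activities to lower quartz exposure during the intervention period. It makes no distinction by arm.

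Under Effect evaluation, the difference between baseline and follow-up in the primary and secondary outcomes "will be compared between the intervention group and the control group". The needs assessment gives the starting level: "The baseline study showed that only 25% of the managers offered this kind of training/education".

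**The concern.** For theme (ii), what is measured and what is supplied are largely the same thing. The outcome asks how much training employees are offered, and the trial brings training into one arm only. The request not to start other activities can also discourage control companies from offering quartz training of their own. Both features push the comparison in the same direction.

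The questionnaire is meant to describe company policy, and the Discussion expects the organisational outcomes to be informative at company and policy level. If theme (ii) rises in intervention companies, a reader will want to know whether those companies changed what they do. An answer that may include the researchers' sessions cannot show this, and the two sources cannot be separated after the questionnaire has been completed.

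**Working it through.** **Inputs**

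- Eight companies and eight manager questionnaires at baseline (Abstract; Step 1: Needs assessment).
- 25% of managers offered this kind of training at baseline (Factors related to occupational quartz exposure).
- Assumptions, because the article does not give these: a 4:4 split of companies, theme (ii) scored yes/no, and control companies unchanged.

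**The plan's own figure.** 0.25 × 8 = 2 companies, so 2/8 = 25% reproduces. The companion figure also agrees: 5/8 = 62.5%, stated as 63%.

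**Effect of counting study sessions.** With four companies in the intervention arm, each one that moves from no to yes only because its manager counts study sessions adds 1/4 = 25 percentage points to that arm's change. The control change is 0, so this is also the difference in change. If no manager counts the sessions, the difference is 0. If all intervention managers count them, the result depends on where the two baseline 'yes' companies fall:

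| Baseline yes, intervention / control | Follow-up yes, intervention / control | Difference in change | Exact two-sided p at follow-up |
|---|---|---|---|
| 0/4, 2/4 | 4/4, 2/4 | 100 points | 0.429 |
| 1/4, 1/4 | 4/4, 1/4 | 75 points | 0.143 |
| 2/4, 0/4 | 4/4, 0/4 | 50 points | 0.029 |

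The p-values are Fisher's exact test with the margins fixed:

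- 4/4 v 2/4: (6 + 6)/C(8,6) = 12/28 = 0.429
- 4/4 v 1/4: (4 + 4)/C(8,5) = 8/56 = 0.143
- 4/4 v 0/4: (1 + 1)/C(8,4) = 2/70 = 0.029

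**How likely each row is.** Under a 4:4 randomisation, the two baseline 'yes' companies fall one per arm in C(2,1) × C(6,3) = 40 of C(8,4) = 70 allocations. They fall together in a given arm in C(6,2) = 15 of 70. The 75-point row is therefore the most likely, and its p-value is 0.143. The p-values only illustrate scale, since the article names no test for the managers' answers.

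**The other themes.** The sessions do not directly supply written procedures (i) or contractor feedback (iv). For (iii), Step 5 describes the toolbox system as an existing sector scheme with at least 10 obligatory sessions a year, organised by managers to obtain a certificate. The study's three sessions sit inside that scheme, so they need not alter whether a regular schedule exists, and nothing confines the scheme to one arm.

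**The case against.** The strongest reply is that the questionnaire asks about company policy and follows an occupational health and safety management norm. A manager may well leave out sessions led by researchers. Item wording, reference period and completion instructions are not in the article, and an article may leave them to fuller documents. The process evaluation records dose delivered separately, and managers are asked afterwards about other interventions. The primary outcome is measured exposure, which this point does not touch.

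Much of this stands, and it is why the point is a risk with a range that starts at zero. It does not remove the point:

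- The sessions run inside a scheme that managers themselves must organise, so a manager could reasonably count them as training offered.
- The questionnaire was already in use during the needs assessment, before the intervention was designed, and no adaptation for follow-up is mentioned.
- Knowing the dose delivered does not show whether a given manager's answer included it.

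A reader might infer more than the documents support:

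- That toolbox meetings are supplied to intervention companies only. Step 5 contradicts this.
- That the whole organisational outcome improves through delivery. One theme of four is exposed, and no composite score is described.
- That a spurious effect is certain. That depends on wording not shown.
- That a 75-point rise would come with p = 0.029. Those figures belong to different allocations.

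It is also fair to object that counting only training started by the company would collide with the Co-interventions request. The remedy has to allow for that.

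**Conclusion.** The point holds for theme (ii) alone. As described, a between-arm gain in training offered cannot distinguish a change in company policy from delivery of the intervention, and the Co-interventions request may widen the gap from the control side. The possible distortion runs from 0 to between 50 and 100 percentage points, given a 4:4 split, a yes/no item and control companies that do not change. The article speaks of extent, so a graded item would give a different size but the same direction. Whether the distortion occurs depends on how managers read the item. Themes (i), (iii) and (iv) need no change on this ground, and the exposure outcomes are unaffected. The correction is worth making because it is nearly free and has to be in place before the follow-up questionnaire goes out.

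**What to change.** - In the follow-up questionnaire, ask managers in both arms to report training and education apart from any session organised by the 'Relieved Working' study. Because they were asked not to start other activities during the study, also ask about training scheduled, or adopted in company policy, for after it. No study sessions existed at baseline, so the exclusion does not alter what was asked then.
- Count study sessions only under dose delivered in the process evaluation.
- Present theme (ii) descriptively for the eight companies at baseline and follow-up. Interpret it in light of the Co-interventions request, and do not offer it as evidence of an organisational effect.

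The cost is a short addition to the follow-up questionnaire and one sentence in the evaluation plan. The downside is a smaller apparent organisational effect. Theme (ii) may also show little movement in either arm, because the Co-interventions request discourages new activity during the study.

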##### Technical control measures

Observations of the workers are used to assess to what extent technical control measures are used. Construction workers from the intervention and control group are observed throughout their shift on their use of technical control measures and protective equipment.

#### Other variables

Socio-demographic data such as gender, age, education level, job category, job history, and job experience are assessed at baseline measurement.

#### Evaluation

The ‘Relieved Working’ study will be evaluated by an effect evaluation and a process evaluation.

##### Effect evaluation

The potential difference between the baseline and follow-up values in the primary and secondary outcomes will be compared between the intervention group and the control group. Analyses of measurements at individual level (i.e., exposure assessment and questionnaire) will be performed by means of multi-level analyses taking clustering of observations of workers within the same company into account, as well as repeated measurements within one worker
[40]. Due to randomization at company level, the data will be analyzed at three levels: time, worker and company. The multi-level analyses using the follow-up measurement as dependent variable will be adjusted for possible confounding factors, such as education level and job category. These variables will also be checked for effect modification.

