**Methods/Design:**

The intervention was developed according to the principles of the Intervention Mapping protocol, meaning that evidence from the literature was combined with information collected from stakeholders (e.g., construction workers, managers and researchers). The intervention aimed to integrate technical, behavioural and organizational factors. The intervention consists of two plenary meetings for all employers within the company, and individual visits at construction worksites, including specific intervention materials. Additionally, a demonstration session regarding control measures was organized for all managers. The effectiveness of the intervention will be evaluated in a cluster randomized controlled trial among eight construction companies, with measurements at baseline and follow-up. Outcome measures are personal respirable dust and quartz exposure by means of exposure assessment, and behavioural and organizational determinants which will be assessed by means of questionnaires. Additionally, a process evaluation will shed light on whether the intervention (does not) works, and, if so, the reasons for this.

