#### Study population

The study population includes blue collar workers in the construction industry. These workers are recruited through eight companies specialized in either demolishing, concrete drilling, sawing and/or façade maintenance, which are all activities associated with relatively high silica exposure levels. Inclusion criteria for the construction workers are (i) available for the intervention period; (ii) sufficient competency in the Dutch language; and (iii) having signed a written informed consent to participate.

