#### Randomization and blinding

In order to avoid intervention group contamination, to obtain maximal co-operation of managers and construction workers, and to enhance participants' compliance, cluster randomization at the level of the company is considered the best randomization strategy for this study. Randomization is performed by the principal researcher ([name]) using an electronic randomization tool (
http://www.randomizer.org) after the baseline measurement. Because the intervention takes place at the worksites, participating workers, managers, supervisors, as well as researchers/trainers cannot be blinded to the group assignment.

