#### Sample size

The sample size was calculated as the number of workers needed to identify an effect of the intervention on occupational exposure to quartz. A previous intervention study on occupational exposure to wood dust aimed to decrease the exposure by 30%
[34]. Assuming alpha is 0.05 and a power of 80% with a possibility to detect at least a 30% change in exposure in our intervention group, a sample size of 42 workers is needed. Although no specific information about exposure trends exists, it is well known that most occupational exposures show long-term downward trends of a few percent annually over recent decades
[35]. Assuming this is also the case for the Dutch construction industry, a decline in exposure in the control group over the course of this study was taken into account. Based on these calculations, and taking into account a loss-to-follow-up of 20%, it was estimated that 60 construction workers are necessary in both the intervention and control group.

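### With eight randomised companies, the effect evaluation describes two different models, and neither is sure to hold the 5% level unless its company-level variation and degrees of freedom are specified

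*Protocol article*

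**What the plan says.** The abstract describes a "cluster randomized controlled trial among eight construction companies", and under Randomization and blinding "cluster randomization at the level of the company is considered the best randomization strategy for this study". Study design gives two measurement occasions, baseline (T0) and after the intervention (T1).

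The Effect evaluation section first sets the contrast: the change from baseline to follow-up, compared between arms. It then promises multilevel analyses "taking clustering of observations of workers within the same company into account, as well as repeated measurements within one worker" and, because companies are randomised, that "the data will be analyzed at three levels: time, worker and company". The sentence after that has the multilevel analyses take the follow-up value as outcome, adjusted for possible confounders such as education and job category.

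The section names no list of random effects, no estimation method, no reference distribution and no degrees of freedom. The Sample size section fixes the nominal level ("Assuming alpha is 0.05 and a power of 80" per cent) and counts workers only. The limitations in the Discussion do not mention the small number of companies.

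**The concern.** The article offers the three-level structure as its answer to company randomisation, so it matters whether that structure protects the comparison of interest.

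A company intercept absorbs stable differences between companies. It does not absorb a company's own shift between T0 and T1, and such shifts are likely here. By the article's own needs assessment, companies are responsible for the control measures available on site and managers for training. Exposure also depends on indoor work, materials and weather, which workers measured at the same site may share. A shared shift of this kind looks like an intervention effect unless the arm difference is judged against company-to-company variation.

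If follow-up is the outcome instead, the company effect stays in the test, but its variance is estimated from eight companies. A large-sample critical value then treats that estimate as known.

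At stake are the p-value and confidence interval for the primary effect on respirable dust and quartz. A nominally significant result could rest on error bars that are too narrow.

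**Working it through.** **Inputs.** From the documents: 8 companies, randomised by company; two occasions; alpha 0.05; 60 workers per arm with 20% loss. Assumed: two-sided test, 4:4 split, equal company sizes, normal log exposure, and the ICC ρ, for which no value is given. Workers per company after loss: 60 × 0.8 = 48 per arm, and 48 / 4 = 12. Between-company degrees of freedom: 8 − 2 = 6.

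**The plan's own figure.** The Sample size section states "a sample size of 42 workers is needed" to "detect at least a 30% change in exposure in our intervention group". Loss alone gives 42 / 0.8 = 52.5, so 53, not 60; the section also allows for a decline in the control group. Reading 42 as per arm, the implied log-scale SD is 0.583. With that SD a 2% control decline gives 48, and 48 / 0.8 = 60. So 60 is compatible with the text but cannot be reproduced without the SD and the trend. It is used here only to obtain 12 workers per company.

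**Reading A: T0 and T1 both outcomes, company and worker intercepts only.** For worker i in company j at time t:

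Y_ijt = β0 + β1·arm + β2·t + β3·arm·t + u_j + v_ij + e_ijt

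The change Y_ij1 − Y_ij0 equals β2 + β3·arm + (e_ij1 − e_ij0). Both u_j and v_ij drop out, so β3 is tested as if worker changes were independent. If changes correlate within companies with ICC ρ, the true variance is larger by 1 + (m − 1)ρ, and

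type I error ≈ 2·[1 − Φ(1.96 / √(1 + (m − 1)ρ))].

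Example with m = 12 and ρ = 0.05: 1 + 11 × 0.05 = 1.55; √1.55 = 1.245; 1.96 / 1.245 = 1.574; error 11.5%.

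**Reading B: follow-up as outcome, company random effect.** The company effect does not cancel. The issue is using z = 1.96 where t on 6 df needs 2.447. When company variation dominates, the limits are:

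- REML: 2·P(t6 > 1.96) = 9.8%.
- ML, which divides the between-company sum of squares by 8 instead of 6: 2·P(t6 > 1.96 × √(6/8)) = 2·P(t6 > 1.697) = 14.1%.

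**Results** (m = 12, 4:4, 200,000 simulated trials per row). ρ is the ICC of change under A and of the follow-up residual under B.

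| ρ | A, formula | A, simulated | B, REML with z | B, ML with z | Company-level t, 6 df |
|---|---|---|---|---|---|
| 0 | 5.0% | 4.9% | 4.1% | 4.9% | 4.9% |
| 0.01 | 6.3% | 6.3% | 4.8% | 6.0% | 5.0% |
| 0.02 | 7.6% | 7.7% | 5.6% | 7.0% | 5.1% |
| 0.05 | 11.5% | 11.6% | 7.0% | 9.1% | 5.0% |
| 0.10 | 17.6% | 17.9% | 8.4% | 11.5% | 5.0% |
| 0.20 | 27.3% | 28.4% | 9.6% | 13.6% | 5.1% |

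With 15 per company (no loss), reading A gives 6.7%, 8.3%, 13.4% and 20.9% at ρ = 0.01, 0.02, 0.05 and 0.10. Fitting the actual random-intercept mixed model in 150 trials per setting (m = 12) rejected in 4.7%, 7.3% and 13.3% at ρ = 0, 0.02 and 0.048. That agrees with the table within the noise of so few runs.

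**After correction.** The company-level t-test holds 4.9–5.1% throughout. REML with a company effect and a 6-df reference gives 1.2% at ρ = 0, rising to 4.8% at ρ = 0.20, so it is conservative when company variance is small.

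**The case against.** The strongest reply is that the article does not specify the test. It names neither ML nor REML, no Wald z, no random-effects list and no degrees-of-freedom method, and it states that clustering will be taken into account. Nothing excludes a company-by-time term or small-sample degrees of freedom, which a journal article commonly leaves to the analysis plan. This stands, and it is why the inflation is a risk and not an established property.

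It does not dispose of the point, because the article does state a structure, and states two that differ. Several shift samples per worker at T1 could supply a lower level under the follow-up model. The article does not describe that, and the level would be shift, not time.

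Three stronger readings are tempting and are not supported:

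- A reader might infer that cancellation and the 6-df problem act together. They belong to different models. Once follow-up is the outcome, nothing cancels and the 18% does not apply.
- A reader might take 7–18% as the error rate of this trial. It depends on an ICC that the article does not give. At zero, reading A holds 5%. At 0.02 or below, REML with z stays at 4.1–5.6%, although ML with z already reaches 7.0% at 0.02.
- A reader might infer that adjusting for job category leaves about 3 degrees of freedom, because the companies are "eight companies specialized in either demolishing, concrete drilling, sawing and/or" façade maintenance. The wording lets one company cover several activities, job category is listed among workers' individual characteristics, and neither the number of categories nor their spread over companies is given.

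**Conclusion.** The point holds as an inconsistency plus a conditional risk. The inconsistency is in the text whatever the ICC: a time level and a single follow-up outcome cannot both describe the primary model. The risk is that either model, fitted with ordinary large-sample inference, gives error bars that are too narrow when companies differ in change or follow-up.

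Under reading A the standard error is too small by a factor √(1 + 11ρ), which is 1.05, 1.10, 1.24 and 1.45 at ρ = 0.01, 0.02, 0.05 and 0.10. Under reading B at ρ of 0.05–0.20 the excess is smaller and bounded, at 9.8% for REML and 14.1% for ML. All of this rests on the assumed 4:4 split, equal company sizes of 12 and the ICC range. Unequal sizes would tend to make it worse. An analysis plan that already carries company variation in change, or in follow-up, and uses small-sample degrees of freedom would remove the risk but not the need to reconcile the two sentences.

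**What to change.** - Name one primary model. Preferably use the follow-up value, adjusted for the worker's own baseline value, with a company random effect. If repeated measures are kept, add a company-by-time random effect.
- Fit by REML with Satterthwaite or Kenward-Roger degrees of freedom, at most 6 less one for each company-level covariate. A company-level t-test on 6 df is an acceptable alternative.
- Add as a check a permutation test over the company allocations that the randomisation allowed. If 4:4 without restriction, there are 70, and the smallest two-sided p is 2/70 = 0.029.
- Correct the sentence on levels to match the chosen model.

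Adjustment for job category can stay as planned.

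The cost is wording and standard software options. For the same standard error the interval widens by 2.447 / 1.96 = 1.25. The capped REML test is also somewhat conservative when company variance is near zero.
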